### Molecular Matching and Molecular Tumor Board/Study Committee

FoundationOne™ results of patients who have genomic alterations detected will be provided to the Molecular Tumor Board, which consists of the study principal investigators, co-investigators, the treating medical oncologist, other medical oncologists, surgical oncologists, radiologist, pathologist, other physicians, scientist specializing in genomics, a genetic counselor, and basic/translational scientists.[9] Since timeliness is essential for managing patients enrolled in this study, a Study Committee, that includes, but is not limited to, the study principal investigators and the treating medical oncologist may provide recommendations on an as needed basis between Molecular Tumor Board meetings in order to avoid delaying treatment. Using the aforementioned molecular aberrations, which represent druggable targets, either through direct pathway inhibition or through an associated pathway (via “crosstalk”), the “molecular individuality” of these tumors will be approached via a customized strategy.[9] Using an “N-of-One” model of precision medicine, the independent Study Committee will make a recommendation for a matched therapy that consists of at least one drug that targets a molecular alteration. Actionability will be limited by our ability to obtain drug(s). We expect 50-70% of patients will have potentially actionable alterations. This percentage is increasing rapidly as we learn more about the pathways and the drugs. We anticipate approximately 40% of patients with actionable alterations will be able to receive molecularly targeted “matched” treatment. These patients will be considered ARM A in each group. Expert opinion, rather than a preconceived algorithm will determine a molecularly matched therapy because a preconceived algorithm [6, 10] will likely be out of date by the time the trial ends. We realize there are downsides to “expert” opinion. However, as a feasibility trial,

we feel that it is a reasonable way to address this issue, and mimics what is done in the community.

Patients for whom we are unable to procure a matched treatment will be considered ARM B in each group. ARM B patients will receive treating physician's choice of traditional systemic chemotherapy treatment for their malignancy, defined by National Comprehensive Cancer Network (NCCN) guidelines and/or tumor board recommendation(s). If there is no standard of care treatment, the treating physician may select a regimen based upon published reports, series, and/or clinical trials.

Patients with no actionable alterations by FoundationOneTM will receive treating physician's choice of traditional systemic chemotherapy treatment for their malignancy, defined by National Comprehensive Cancer Network (NCCN) guidelines and/or tumor board recommendation(s). If there is no standard of care treatment, the treating physician may select a regimen based upon published reports, series, and/or clinical trials.

### **Treatment Decisions**

The Study Committee or Molecular Tumor Board will give suggestions but ultimately the treating physician chooses the treatment, whether matched or unmatched. While flexible choice is not a feature of many protocols, it was a feature of PREDICT and is a feature of WINther.[6] This has the advantage that the flexibility allows the treating physician to make the best informed choice for their patient, mimicking what would happen in the community, as well as making the trial logistically possible. This protocol is flexible and allows for the treating physician to make the best-informed choice for their patient. If a patient has a matched abnormality that suggests that they should receive a targeted agent that is different than an unmatched therapy offered in a clinical trial, the treating physician will have the final decision and not the study PIs. However, this is likely the case only in the previously treated patients because most treatment naïve patients will not be candidates for most clinical trials. **It is our intent to recommend potential therapy based upon the following Levels of Evidence as is being utilized by the NCI-MATCH Trial:**

- Level 1: FDA approved; evidence of target inhibition, or proof of mechanism; demonstration that patient selection with companion diagnostic is more likely to respond.
- Level 2: Agent met a clinical endpoint (objective response, PFS, or OS); with evidence of target inhibition; plausible evidence of a predictive or selection assay/analyte.
- Level 3: Agent demonstrated evidence of clinical activity with evidence of target inhibition; some evidence of a predictive or selection assay/analyte.
- Level 4: Preclinical evidence of anti-tumor activity and evidence of target inhibition; hypothesis for a predictive or selective assay/analyte.

### **In recommending therapies, treatments may include the following:**

- FDA-approved single agents or investigational single agents in umbrella or basket trials.
- Two agents may be utilized if there is data published in peer-reviewed journals or abstract form demonstrating safety and/or efficacy of a two-drug combination.

**But, the treating physician will choose based on his/her knowledge of the medical situation, the test results, and molecular tumor board recommendations. Therefore, all final treatment decisions are the responsibility of the treating physician. This feasibility study will determine whether molecular aberrations, which represent druggable targets, will be offered by treating oncologists to treatment naïve patients with incurable malignancies in order for patients to receive molecularly targeted matched treatment based on genomic analysis.**

### **Evaluation of Treatment Decisions**

Separately, the independent Study Committee will evaluate the degree of matching that occurred using the best information available at the end of the trial. They will be blinded to individual patient outcomes. However, this committee will also rely upon expert opinion rather than a preconceived algorithm, which would likely be out of date by the time the trial ends.

### **Insurance Coverage**

A medication acquisition specialist will liaise and negotiate with insurance carriers to obtain authorization to prescribe matched regimens. If we cannot obtain insurance coverage for the matched therapy, the patient will receive their physician's choice of traditional systemic chemotherapy. **We will make all efforts to secure matched therapy, but this cannot be promised. If an insurance carrier denies the matched therapy, the patient will still receive their physician's choice of traditional systemic chemotherapy.**

### **Summary**

Treatment will be selected and performed by the patient's treating physician and will not fall under the auspices of this study protocol. Drugs will be administered according to the guidelines found in the product label and the treating physician will account for special precautions or warnings relevant for each drug administered (e.g., incompatibility of agent with commonly used intravenous solutions, necessity of administering agent with food, pre-medications, hydration, whether any monitoring of vital signs during or shortly after treatment is required, etc.). Patients treated as part of clinical interventional clinical trials will be consented and treated according to the clinical study protocol. Regarding the recommended therapy regimen, the Study Committee, blinded to outcomes, will assess whether or not matching occurred. This determination will indicate whether the patient is Arm A or B.

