### **Endpoints**

#### **Primary Endpoint:**

The proportion of patients who receive molecularly targeted matched treatment **after recommendations** based on genomic analysis

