### **Prohibited concomitant therapy**

Investigational-targeted therapies may be used while the patient is on the study if they are the appropriate matched therapy for the patient's disease. If additional un-matched anti-cancer agents are administered in combination with matched therapy, then the patient will no longer be considered to be on matched therapy unless the patient already received that unmatched therapy and did not achieve a PR or CR.

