- The results of PFS and OS outcomes will be described relative to historical controls or published data. Due to the potential difference in patient populations between the current study and historical controls, we will also perform multivariate analyses to adjust the difference in prognostic factor(s) when comparing the PFS and OS between the different cohorts.
- The treatment grade 3-5 adverse events will be documented and analyzed by descriptive statistics.

As described earlier, this is a feasibility and descriptive study that will generate preliminary data for designing future studies. The exact numbers of patients in Arm A and Arm B for each group correspond to the feasibility endpoints. Although these numbers are unknown in the design stage, with the comprehensive genomic profiling and dedicated efforts in finding and securing the matched therapy, we expect that 40% of the patients (N=30) will be in Arm A and 60% of the patients (N=45) will be in Arm B for all three patients groups.

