## **7.6 Obligations of Investigators**

The Principal Investigators are responsible for the conduct of the clinical trial at the site in accordance with Title 21 of the Code of Federal Regulations and/or the Declaration of Helsinki. The Principal Investigators are not responsible for personally overseeing the treatment of all study patients. This is the responsibility of the treating physician. The Principal Investigator must assure that all study site personnel, including sub-investigators and other study staff members, adhere to the study protocol and all FDA/GCP/NCI regulations and guidelines regarding clinical trials both during and after study completion.

The Principal Investigators will be responsible for assuring that all the required data will be collected and entered onto the Case Report Forms. Periodically, monitoring visits will be conducted and the Principal Investigator will provide access to his/her original records to permit verification of proper entry of data. At the completion of the study, all case report forms will be reviewed by the Principal Investigators and will require his/her final signature to verify the accuracy of the data.

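### The Arm A/B label behind the primary endpoint is set by a committee described as blinded that includes the treating oncologist, and no section says when the label is fixed

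*Protocol*

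**What the plan says.** - **Endpoint.** Section 1.5 gives the primary endpoint as "The proportion of patients who receive molecularly targeted matched treatment" after recommendations based on genomic analysis. Section 6.4 adds: "The exact numbers of patients in Arm A and Arm B for each group correspond to the feasibility endpoints".
- **Who sets the arm.** The Summary at the end of the treatment-selection text in Section 3.2 says "the Study Committee, blinded to outcomes, will assess whether or not matching occurred", and then: "This determination will indicate whether the patient is Arm A or B".
- **Who sits on the committee.** Section 3.2, Molecular Matching and Molecular Tumor Board/Study Committee, gives an open-ended membership that names two roles: "the study principal investigators and the treating medical oncologist may provide recommendations". The same section calls the committee independent and has it recommend the matched therapy.
- **End-of-trial review.** Section 3.2, Evaluation of Treatment Decisions, describes a separate review of the degree of matching, "using the best information available at the end of the trial". It rests on expert opinion, and members are to be blinded to individual outcomes.
- **Loss of matched status.** Under Prohibited concomitant therapy (Section 3.5), if unmatched agents are given in combination with matched therapy, "then the patient will no longer be considered to be on matched therapy". The exception is an agent the patient had already received without a partial or complete response.
- **Another rule.** Section 6.1 assigns the arm by the therapy received and mentions no adjudication.

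**The concern.** The safeguard claimed for the label is that those who set it do not know how the patient fared. The stated membership contradicts this. Because the same label gives the primary count and splits patients for response, PFS and OS, any influence of outcome on it reaches both the feasibility result and the exploratory comparisons.

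The missing time point makes this matter. A label fixed when the first regimen starts could not be affected by response, whoever sat on the committee. With no date, and with three bases for the label that can disagree, the text allows classification or reclassification after the week-8 scan.

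**Working it through.** **1. Can the committee be blind as constituted?**

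- Treating oncologist: chooses the therapy (Section 3.2, Treatment Decisions). For Groups 1 and 2 Arm A and for Group 3 Arm A, the week-8 RECIST result guides what follows. This member necessarily knows that patient's response.
- Principal investigators: told of serious adverse events within 24 hours (Section 5.4.4). At study completion "all case report forms will be reviewed by the Principal Investigators" (Section 7.6). The form review shows knowledge of outcomes only at the end, and Section 7.6 also says they do not personally oversee every patient's treatment. Their case is weaker than the treating oncologist's.
- No other composition of the Study Committee is given.

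**2. Do the label rules agree?**

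| Place | Basis for the label | Time point |
|---|---|---|
| 3.2 Summary | Committee judgement on the recommended regimen | None |
| 3.5 | Matched status lost when unmatched agents are combined with matched therapy | None |
| 6.1 | Therapy received | None |

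A patient who receives matched therapy and later has an unmatched agent added is Arm A under 6.1, no longer on matched therapy under 3.5, and undetermined under the Summary.

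**3. The plan's own figure.** Section 6.4 states 79% power for response rates of 0.25 and 0.05 with 30 and 45 patients, one-sided 10%, continuity-corrected chi-square.

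- Pooled rate: (30×0.25 + 45×0.05)/75 = 0.13
- SE under the null: √[0.13×0.87×(1/30+1/45)] = 0.0793
- SE under the alternative: √[0.25×0.75/30 + 0.05×0.95/45] = 0.0855
- Continuity correction: 0.5×(1/30+1/45) = 0.0278
- Power: Φ[(0.20 − 0.0278 − 1.2816×0.0793)/0.0855] = 79.6%

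The figure reproduces. It presumes arms that are fixed and correctly labelled.

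**4. Response comparison if labels move.** Assume equal true response rate r, and that a fraction f of Arm A non-responders moves to Arm B. Both r and f are assumptions.

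Rate in A = 30r / [30 − 30(1−r)f]; rate in B = 45r / [45 + 30(1−r)f].

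| r | f | Arm A | Arm B | Gap (points) |
|---|---|---|---|---|
| 0.15 | 0.1 | 4.5/27.45 = 16.4% | 6.75/47.55 = 14.2% | 2.2 |
| 0.15 | 0.2 | 4.5/24.9 = 18.1% | 6.75/50.1 = 13.5% | 4.6 |
| 0.15 | 0.3 | 4.5/22.35 = 20.1% | 6.75/52.65 = 12.8% | 7.3 |
| 0.20 | 0.1 | 6/27.6 = 21.7% | 9/47.4 = 19.0% | 2.7 |
| 0.20 | 0.3 | 6/22.8 = 26.3% | 9/52.2 = 17.2% | 9.1 |

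Simulating the planned test with no true difference (200,000 runs per setting), the false-positive rate against a nominal 0.10 is:

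| Common rate | 0 moved | 3 moved | 6 moved | 9 moved |
|---|---|---|---|---|
| 0.15 | 0.06 | 0.10 | 0.18 | 0.27 |
| 0.25 | 0.06 | 0.13 | 0.26 | 0.41 |

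**5. Primary count if labels are lost.** Section 5.1 defines success as at least 40% matched (N ≥ 30) in each group. Section 6.2 expects 30 in Arm A and 45 in Arm B, so 75. If a share l of Arm A loses the label, P(success) = P[Bin(75, p(1−l)) ≥ 30].

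| True share p | l = 0 | 5% | 10% | 20% |
|---|---|---|---|---|
| 0.40 | 0.54 | 0.40 | 0.27 | 0.09 |
| 0.45 | 0.84 | 0.72 | 0.58 | 0.27 |

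The threshold sits at the expected share, so one patient turns 30/75 (40.0%) into 29/75 (38.7%), which fails. This uses the stated 75 per group. Section 6.2 allows up to 1000 patients in Group 3, where one patient would count for less.

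**The case against.** A good deal of the opposing case stands.

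- **Hindsight.** A reader might infer that end-of-trial knowledge decides the primary numerator. The text does not say so. Evaluation of Treatment Decisions introduces that review as separate and ties it to the degree of matching, whereas the yes/no arm call in the Summary carries no date. Later knowledge may feed into the label, but this is not stated.
- **Later additions.** A reader might infer that adding a drug moves a patient to Arm B. Section 3.5 names neither Arm B nor the primary count, and a regimen combined from the start also fits its wording. A later addition does not plainly undo receipt of matched treatment.
- **One-way bias.** A reader might infer that the label favours matched therapy. In Groups 1 and 2, patients with stable or progressive disease are generally switched to chemotherapy, with matched therapy continued where no effective regimen exists. A switch is not a combination, so it does not trigger Section 3.5. The exception there also keeps some patients matched, and a combination given up front could remove responders. Nothing in the protocol shows that loss of status follows poor response.
- **Context.** The trial is descriptive, and A-versus-B is exploratory and non-randomized, with the arm depending on drug access and insurance. It is confounded whatever the label rule. The protocol openly accepts the drawbacks of expert opinion, so the lack of an algorithm is not a defect here.
- **Timing.** An SAP, which is not at hand, might date the label.

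What this does not answer is the contradiction inside the protocol: a committee said to be blind to outcomes has a member who cannot be. The label it sets is the primary endpoint, not only an exploratory split.

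**Conclusion.** The concern holds in this form. The claims of independence and blinding conflict with the stated membership, clearly so for the treating oncologist. The sections on the label differ in basis and none fixes its timing, so as written the label could be set or altered once response is known.

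No stated figure is shown to be wrong, and no direction of bias is established. Loss of matched status works against declaring feasibility, while selective loss among non-responders would favour Arm A on response. The 2-to-9-point gap and the changes in error rate and success probability rest on assumed reclassification rates; they show sensitivity, not expected error. The change should be made because it is cheap and closes a route from outcome to the primary count.

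**What to change.** - **Section 3.2, Summary.** Define the arm for analysis from the first post-recommendation regimen as started. Classify it before the first response scan, using only the genomic report, the board recommendation and the drug list. The treating oncologist and any member holding that patient's outcome data do not vote; scientists and pathologists already on the board can.
- **Patients already treated.** Members without outcome data classify from the same documents.
- **Section 3.5.** State that agents added after the first regimen starts do not change the analysis arm.
- **Section 6.1.** Refer to the same definition.
- **Evaluation of Treatment Decisions.** Keep the end-of-trial degree-of-matching review as a sensitivity analysis.

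This concerns analysis labels only and leaves treatment untouched. The cost is wording and an earlier date for an existing review, with no new staff. The downside is that mismatches learned later appear only in the sensitivity analysis.

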### **Study Group 1 and Group 2 (treatment naïve)**

ARM A:

A matched treatment regimen will be administered for approximately 8 weeks as dictated by recommendations for approved anti-cancer agents or as dictated by clinical trials. Disease-appropriate imaging (i.e., PET-CT vs. CT vs. MR imaging) will be performed at approximately week 8 according to standard of care or required clinical trial practices. Objective tumor response will be determined according to RECIST v1.1 and this First Response assessment will guide subsequent treatment according to the following:

3. Patients demonstrating a PR or CR per RECIST 1.1 will continue treatment until
  - a complete response persists for at least six months
  - the tumor becomes resectable
  - their tumor response declines to SD or PD
  - they experience unacceptable toxicity.

4. Patients demonstrating SD or PD per RECIST 1.1 will be removed from matched therapy and placed onto the treating physician's choice of systemic chemotherapy appropriate to their disease. Alternatively, the treating physician may continue matched therapy at their discretion if there are no effective traditional systemic chemotherapy regimens available.

Patients who experience SD but short of PR while on matched treatment may, after experiencing progressive disease while receiving treating physician's choice of systemic chemotherapy appropriate to their disease, return to their prior matched treatment and will be monitored again for benefit. The degree of objective tumor response observed at the patient's First Response Assessment on the original matched treatment, will then guide subsequent treatment according to the following:

1. Patients demonstrating a 10-29% decrease in the sum of diameters of target lesions (First Response Assessment) will resume treatment with the original matched treatment regimen. Treatment will continue until:
  - a complete response persists for at least 6 months,
  - their tumor becomes resectable,
  - they experience progressive disease (PD), or
  - they experience unacceptable toxicity.
2. Patients demonstrating a <10% decrease in the sum of diameters of target lesions (First Response Assessment) will then receive the traditional second-line standard of care treatment appropriate for their disease.

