| Duration of administration            | 
Arm A
 
 
• Groups 1 and 2 = <math>\sim 8</math> week cycles of a regimen of <math>\geq 1</math> drug that targets molecular alteration(s) followed by disease appropriate imaging (i.e., PET-CT vs. CT vs. MR imaging) followed by crossover to treating physician's choice of systemic chemotherapy for SD or PD per RECIST, or unacceptable toxicity but to remain on I-PREDICT recommended regimen if CR, PR by RECIST 1.1
 
• Group 3 = <math>\sim 8</math> week cycles of a regimen of <math>\geq 1</math> drug that targets molecular alteration(s) followed by disease appropriate imaging (i.e., PET-CT vs. CT vs. MR imaging) with cessation of therapy if PD or unacceptable toxicity
 
 
Arm B
                                                                                                                                                                                                                                                                                                                                                                                                                                                                                                                                |

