#### **Exploratory Endpoints**

Estimate the:

1. Overall response rate (ORR) defined as partial (PR) or complete response (CR) occurring at any point during treatment according to Response Criteria in Solid Tumors (RECIST) 1.1 in all treatment groups
2. Regression rate as a percent defined by best percent size reduction in target lesions from baseline to discontinuation in all groups
3. Progression free survival (PFS) defined as time from first dose to disease progression or death, whichever occurs first
4. Overall survival (OS) defined as time from first dose to death due to any cause
5. Resection rate as a percent of patients previously considered unresectable that are able to be resected in all groups
6. Change in biochemical tumor markers of disease as defined as the best percent change from baseline in relevant tumor markers from first dose to discontinuation
7. Incidence of serious adverse events in all groups according to CTCAE v4.03

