### **Progression-Free Survival**

Progression-free survival (PFS) is defined as the duration of time from the start of a treatment until objective tumor progression or death.

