## **6.4 Sample Size Calculation**

All exploratory analysis will test the hypothesis of greater response rate in Arm A than that in Arm B. With an estimated sample size of 30 (ARM A) and 45 (ARM B) in each group, we can estimate the response rate with a standard error no larger than 0.09 and 0.07, respectively. We will have sufficient statistical power to detect the difference between groups only if the difference between groups is sufficiently large. For example, with the sample size of 30 and 45 for Arm A and Arm B, we will have 79% power to detect the response rate of 0.25 and 0.05 between the two arms with one-sided 10% type I error rate using the continuity corrected chi-square test.

We will have more than 80% power to detect the difference between Arm A and Arm B using the log-rank test when the median PFS is 4 months and 2 months for the two arms, respectively.

In addition, in Group 1A, we will estimate the proportion of patients who are initially unresectable (as deemed by two surgeons) but converted to resectable (as deemed by two surgeons) after 8 weeks of the matched treatment, or if ever resected. With 30 patients, we expect to see at least one patient becomes resectable with a probability of 0.79, 0.96, and 0.99 if the conversion rate is 0.05, 0.10, and 0.15, respectively. We expect to see at least 2 patients become resectable with a probability of 0.82 and 0.95 if the conversion rate is 0.10 and 0.15, respectively. One-sided nominal level at 10% will be used to declare statistical significance. No P value adjustment for multiplicity will be applied due to the exploratory nature of the study. All study results need to be confirmed by future studies with larger sample sizes.

- The response rate (proportion of patients reaches CR or PR) will be estimated based on RECIST for each patient group and each treatment arm.
- The tumor regression rate (in %) will be calculated by the percent tumor size reduction from baseline to after treatment will be determined in and across patient groups.
- Progression-free survival (PFS) and overall survival (OS) will be determined in and across patient groups and treatment arms.

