### **Analysis Plan for Group 1 and Group 2**

- The treatment efficacy in the matched cohorts (i.e., Groups 1A and 2A) and in the cohort of patients receiving treating physician's choice of traditional systemic chemotherapy [i.e., no drug(s) available for target(s), no insurance coverage for recommended drug(s) = Group 1B and 2B, respectively] will be described.
- For the unresectable patients, determine whether the resectability rate in Group 1A is higher than in Group 1B.

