## 2.3 Evaluation of best overall response

The best overall response is the best response recorded from the start of the study treatment until the end of treatment taking into account any requirement for confirmation. On occasion a response may not be documented until after the end of therapy so protocols should be clear if post-treatment assessments are to be considered in determination of best overall response. Protocols must specify how any new therapy introduced before progression will affect best response designation. The patient's best overall response assignment will depend on the findings of both target and non-target disease and will also take into consideration the appearance of new lesions. Furthermore, depending on the nature of the study and the protocol requirements, it may also require confirmatory measurement. Specifically, in non-randomized trials where response is the primary endpoint, confirmation of PR or CR is needed to deem either one the 'best overall response'. This is described further below.

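### In Groups 1A and 2A, PFS, OS and the ever-resected rate run past a planned week-8 switch to chemotherapy, so they describe a treatment sequence but are compared with Arm B as matched versus unmatched therapy

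*Protocol*

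**What the plan says.** Protocol section 3.2 (Study Group 1 and Group 2, Arm A) uses imaging at about week 8 to decide what follows: "Patients demonstrating SD or PD per RECIST 1.1 will be removed from matched therapy and placed onto the treating physician's choice of systemic chemotherapy". There is one exception: "the treating physician may continue matched therapy at their discretion if there are no effective traditional systemic chemotherapy regimens available". The Study Summary gives the same rule, with matched therapy "followed by crossover to treating physician's choice of systemic chemotherapy for SD or PD per RECIST". Physician's-choice chemotherapy is also what Arm B receives from the start.

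Section 6.1 assigns the arm by whether matched therapy was received. No text reassigns a patient after the switch.

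The endpoints run on:
- **PFS.** Section 1.5 reads "Progression free survival (PFS) defined as time from first dose to disease progression or death, whichever occurs first". Section 5.2 gives "the duration of time from the start of a treatment until objective tumor progression or death". Neither ends the clock at a switch made for stable disease.
- **OS.** It runs from first dose (or start of treatment) to death.
- **Resection.** Section 6.4 counts Group 1A conversions "after 8 weeks of the matched treatment, or if ever resected". The Study Summary likewise allows week 8 or any later time.

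Sections 6.4 and 6.6 plan a log-rank comparison of PFS between Arms A and B. Section 6.6 also sets out to "determine whether the resectability rate in Group 1A is higher than in Group 1B".

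**The concern.** A Group 1A or 2A patient with stable disease at week 8 has had no PFS event. From then on, PFS time accrues on the kind of treatment that defines Arm B, but it is reported for the matched cohort. A conversion to resectable disease under that chemotherapy counts in the 1A rate in the same way. Patients who switch for progressive disease already have their PFS event, but they can still add to OS and ever-resected.

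The protocol bounds other situations. Regression stops at discontinuation (section 1.5), and section 3.5 deals with unmatched agents given in combination with matched therapy. It sets no boundary for a later, sequential switch. Group 3 Arm A has no written switch to chemotherapy for stable disease, so across-group PFS descriptions also mix two kinds of outcome.

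Section 1.3 intends the results to inform the design of randomised trials. A sequence result read as a matched-therapy result would carry a wrong effect size into those designs.

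**Working it through.** **Inputs from sections 6.2, 6.4 and 6.6.** 30 Arm A and 45 Arm B patients per group; median PFS 4 versus 2 months; Arm A response 0.25; one-sided 10% level; 30 months of accrual plus 6 of follow-up; Group 1A conversion rates of 5%, 10% and 15%.

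**Assumptions.** Exponential PFS, all responses by week 8, no use of the exception, and post-switch chemotherapy medians of 2 to 6 months.

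**1. The plan's own figures reproduce.** With uniform accrual, expected PFS events are 30 × 0.932 + 45 × 0.988 = 72.4. Log-rank power (Schoenfeld) is Φ(√(72.4 × 0.4 × 0.6) × ln 2 − 1.282) = Φ(1.61), about 0.95, which agrees with the stated power above 80%. The chance of at least one conversion in 30 is 1 − 0.95³⁰ = 0.785, 1 − 0.90³⁰ = 0.958 and 1 − 0.85³⁰ = 0.992, against the stated 0.79, 0.96 and 0.99. The arithmetic is sound; the issue is what is being measured.

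**2. Who switches without an event.** Eight weeks is 56/30.44 = 1.84 months. Progression-free at week 8: 0.5^(1.84/4) = 0.727. Less responders: 0.727 − 0.25 = 0.477, and 0.477 × 30 = 14.3 patients. That is 0.477/0.727 = 66% of those still progression-free.

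**3. Effect on Arm A PFS.** For t beyond week 8 and post-switch median m,
S(t) = 0.25 × 0.5^((t − 1.84)/4) + 0.477 × 0.5^((t − 1.84)/m).
For m = 2, S(3.17) = 0.199 + 0.301 = 0.50, so the median is 3.2 months.

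Mean PFS time splits into (1 − 0.727) × 4/ln 2 = 1.58 months before week 8, 0.25 × 4/ln 2 = 1.44 for responders afterwards, and 0.477 × m/ln 2 on chemotherapy. For m = 2 the chemotherapy share is 1.38/(1.58 + 1.44 + 1.38) = 31%.

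The last two columns are the probability of a significant log-rank result, from 4,000 simulated trials per scenario (standard error at most √(0.25/4000) = 0.008). The no-effect column uses a matched median of 2 months, equal to Arm B, and matched response rates of 5% to 25%.

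| Post-switch median (months) | Arm A median (months) | Arm A PFS time on chemotherapy | Matched median 4 months | No matched effect |
|---|---|---|---|---|
| 2 | 3.2 | 31% | 0.68 | 0.10 |
| 3 | 3.6 | 41% | 0.85 | 0.21–0.30 |
| 4 | 4.0 | 48% | 0.93 | 0.30–0.50 |
| 6 | 4.6 | 58% | 0.98 | 0.46–0.73 |

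For reference, with PFS censored at the switch these probabilities are about 0.83 and 0.09–0.10 whatever the chemotherapy does. Such censoring may be informative, so it serves here only to isolate the effect of the switch.

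**4. Effect on ever-resected.** Suppose matched therapy converts nobody and chemotherapy converts 5%, 10% or 15% of the stable-disease patients who switch. The Group 1A rate is then 0.477 × 0.05, 0.10 or 0.15 = 2.4%, 4.8% or 7.2%. The chance of at least one conversion in 30, 1 − (1 − p)³⁰, is 0.52, 0.77 or 0.89. Counted only up to the switch, it is zero.

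**The case against.** Several counter-arguments carry weight.

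- **Exploratory status.** All affected endpoints are exploratory. The protocol calls itself hypothesis-generating, describes 1A/2A and 1B/2B efficacy rather than resting a decision on it, and asks for confirmation in larger studies. The primary endpoint, the proportion receiving matched treatment, cannot change with the switch. This stands and limits the importance of the point.
- **Treatment policy and the SAP.** Following PFS through a planned switch is a recognised strategy, section 6.1 speaks of testing a strategy, and censoring rules often sit in a SAP. This stands in part. The definitions and the arm comparison are nevertheless fixed in the protocol, and the arms are labelled by therapy rather than by strategy.
- **Direction for PFS.** A reader might infer that the switch favours Arm A on PFS in general. The documents do not support that: at the protocol's own Arm B median of 2 months, it works against Arm A.
- **Response.** A reader might also infer that the response rate is inflated, and Appendix A section 2.3 says "Protocols must specify how any new therapy introduced before progression will affect best response designation". But response is counted during treatment, best response runs to the end of treatment (section 5.2), and regression stops at discontinuation. The Appendix sentence is generic guideline text about best response and says nothing on PFS or resection.
- **The 48%.** The rates behind it are one example applied to every group, and they resemble the 27% versus 5% that section 1.3 quotes for heavily pretreated patients. Use of the exception, or responses after week 8, would change the share. It is an illustration towards the upper end.
- **Truncating 1A only.** Setting a before-switch resection rate in 1A against an open-ended rate in 1B would reverse the bias. This stands and shapes the fix.

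**Conclusion.** The point holds for PFS, OS and ever-resected in Groups 1A and 2A. As written, these measure matched therapy followed by chemotherapy in every patient switched for stable disease, while the planned comparisons present them as matched versus unmatched.

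For ever-resected, later chemotherapy can only raise the Arm A rate. For PFS the result is misattributed rather than biased in one known direction: the false-positive rate may reach about 21–50% at post-switch medians of 3 to 4 months, or power may fall to about 0.68 at 2 months. These sizes rest on exponential PFS, the illustrative rates and assumed chemotherapy medians. That the endpoints run past the switch rests on the text alone.

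The week-8 resection rate, response, regression and the primary feasibility endpoint are not affected. The correction is worthwhile and cheap, but the trial's main conclusion does not depend on it.

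**What to change.** Leave the treatment rule as it is and change only the analysis wording in sections 1.5, 6.4 and 6.6:

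1. Base the 1A versus 1B resectability comparison on the week-8 rate in both arms. The Study Summary already plans that rate.
2. Report ever-resected in 1A descriptively, split into before and after the switch.
3. Label PFS and OS from first dose in 1A and 2A as outcomes of the sequence of matched therapy then chemotherapy. Add time to failure of matched therapy (progression, death or switch) as a description within Arm A only. It should not be compared with Arm B, because stable disease triggers the switch only in Arm A.

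The cost is a few sentences and slightly more reporting. The dates are needed anyway, because the serious adverse event window in section 5.4.1 depends on regimen discontinuation and the start of new therapy. Arm A figures may look less favourable.
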